### Sample size

2.13

To accomplish the aim of this project it was calculated the sample size based on the effect size reported by Cavalheri and Granger (2017) [36] of preoperative exercise training in pulmonary complications after lung resections (0.33) and considering an α = 0.05 and a statistical power of 95%, the required sample is 180 patients, 45 for each group (G∗Power version 3.1.9.2; Universität Düsseldorf, Germany) [37]. However, assuming a percentage of dropouts around 10%, our study's estimated total sample size will be 200 patients (50 in each study arm).

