## Introduction

1

Lung cancer is the leading cause of cancer death globally, [1]. In 2022, it accounted for roughly 12.4% of all cancer diagnoses and 18.7% of all cancer-related deaths [2].

Lung resection is the *gold standard* and the most effective treatment for lung cancer, especially in early-stage non-small cell lung cancer (NSCLC), improving long-term survival and quality of life [3]. However, only 15-20% of patients diagnosed with lung cancer are eligible for lung resection [3].

Although the well-known benefits of lung resection, it carries a considerable risk of postoperative pulmonary complications (PPC) occurrence, which negatively impact patients' morbidity and mortality, and escalate hospital costs [4,5]. Previous evidence has suggested that patients with superior functional capacity are better prepared to cope with the stress induced by surgery and, thus, less susceptible to PPCs [6]. The growing body of evidence from randomized controlled trials supports the efficacy of prehabilitation in reducing both the incidence and severity of PPCs and shortening the length of hospital stay (LOS) [[7], [8], [9]].

Prehabilitation lasts the time gap between the decision to proceed with surgery and the surgery. It aims to improve patients’ functional capacity by implementing a multimodal approach that includes medical optimization, physical exercise, nutritional and psychological support [6]. The guidelines for the enhancement of recovery after lung surgery highlight that the preoperative phase should consist of education and counselling, preoperative nutrition, smoking cessation (at least 4 weeks before surgery), alcohol dependency management, anaemia management, and pulmonary rehabilitation and prehabilitation [10].

A meta-analysis encompassing randomized controlled trials showed that patients receiving exercise prehabilitation programs had a lower odds ratio of PPCs (0.31; CI95%: 0.20; 0.48; I^2^ = 0%) and LOS (−3.02; CI95%: −4.82; −1.22; I^2^ = 85%), in comparison with patients who did not receive any intervention [11].

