### Primary outcomes

2.10

PPC (from surgery to 30 days after discharge) will be screened according to the joint agreement and standardized definitions provided by the European Society of Thoracic Surgery (ESTS) and the Society of Thoracic Surgeons (STS) [20].

LOS and readmissions (from surgery to 30 days after discharge) will be based on the number of postoperative hospitalization days, including hospital readmissions related to surgery, assessed in clinical data. For those patients with persistent air leak, allowed to return home with a drainage tube, it be resisted the number of days util remove the tube.

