### Statistical analysis

2.14

A framework for testing superiority will be applied. In the primary analyses, we will compare the effectiveness of both exercise interventions to usual care (no exercise training). Final analyses will be conducted after the collection and processing of data for the primary and secondary outcomes. The time points for data collection of each outcome are outlined in the outcomes section.

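### The stated 180 patients at 95% power does not follow from the inputs given, and 95% power for PPC in each programme against control is unsupported

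*Protocol article*

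**What the plan says.** Section 2.13 (Sample size) bases the calculation on a published effect "of preoperative exercise training in pulmonary complications after lung resections (0.33"). With alpha 0.05 it states "a statistical power of 95%, the required sample is 180 patients, 45 for each group", computed in G*Power, and raises this to 200 (50 per arm) for about 10% dropout.

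The section does not say whether 0.33 is a risk ratio, an odds ratio, a risk difference or a standardised effect. It does not name the test, its sidedness, the comparison powered or the PPC risk expected in controls.

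Three other places bear on the point:

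- **Outcome.** Section 2.10 and Table 1 define PPC by occurrence from surgery to 30 days after discharge, which is a yes/no outcome.
- **Comparison.** Section 2.14 says "we will compare the effectiveness of both exercise interventions to usual care (no exercise training"), in a superiority framework. The hypothesis in the Introduction is also framed as prehabilitation groups against control.
- **Scale.** The only effect of prehabilitation on PPC whose scale is named is in the Introduction, where a meta-analysis of exercise programmes "had a lower odds ratio of PPCs (0.31; CI95%: 0.20; 0.48"). It is a different source from the one cited for 0.33.

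**The concern.** A sample-size statement should let a reader get from its inputs to its N. Here one unlabelled number, an alpha and a power are said to give 180, and the standard four-group calculations that accept a single effect size do not return 180.

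The larger matter is the 95%. For a binary outcome compared between two arms, a risk ratio or an odds ratio fixes the power only together with a control risk, and none is given. If the trial finds no difference in PPC, readers will set that result against a claimed 95% power and may take it as strong evidence of no effect. At control risks of 20% to 30% the chance of detecting the planned effect in one comparison may be nearer one half to two thirds.

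**Working it through.** **Inputs from section 2.13.** Effect 0.33, alpha 0.05, power 0.95, N = 180 (45 per arm), dropout 10%. **Assumed, because not stated:** two-sided testing, no multiplicity adjustment, and control PPC risks shown over a range.

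**Step 1: dropout.** 180 / (1 − 0.10) = 200. This step is correct.

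**Step 2: try to reproduce 180 with four groups.**

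- *One-way F test, f = 0.33.* The noncentrality is λ = N·f², with 3 and N − 4 df. At N = 161, λ = 161 × 0.1089 = 17.53 and power is 94.9%. At N = 162, λ = 17.64 and power is 95.05%. So N = 162, or 164 with equal arms (41 each, power 95.3%).
- *Chi-square, 3 df, w = 0.33.* λ = N·w². At N = 157 power is 94.9%. At N = 158, λ = 17.21 and power is 95.04%. So N = 158 (160 with equal arms).
- *At N = 180,* λ = 19.60, and power would be 96.9% (F) or 97.2% (chi-square).
- *Working back from 180,* the effect would have to be f ≈ 0.312 or w ≈ 0.309.
- *Other variants.* ANCOVA gives 162, and repeated-measures forms give 154 or fewer. Alpha 0.025 gives 185 and alpha 0.05/3 gives 198. A two-sample t test with d = 0.33 needs about 240 per arm. None gives 180.

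**Step 3: power for one programme against control on PPC.** With control risk p₁, programme risk p₂, mean p̄ = (p₁ + p₂)/2 and n = 45 per arm:

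power = Φ{ [ |p₁ − p₂| − 1.96·√(2p̄(1 − p̄)/n) ] / √( [p₁(1 − p₁) + p₂(1 − p₂)]/n ) }

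*0.33 as a risk ratio*, p₂ = 0.33·p₁. Example at p₁ = 0.30: p₂ = 0.099, difference 0.201, p̄ = 0.1995, null SE 0.0842, alternative SE 0.0815. Then (0.201 − 1.96 × 0.0842)/0.0815 = 0.44, and Φ(0.44) = 67%.

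*0.33 as an odds ratio*, p₂ = x/(1 + x) with x = 0.33·p₁/(1 − p₁). Example at p₁ = 0.30: p₂ = 0.124, difference 0.176, null SE 0.0862, alternative SE 0.0841. Then (0.176 − 1.96 × 0.0862)/0.0841 = 0.09, and Φ(0.09) = 53%.

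| Assumed control risk | 20% | 30% | 40% | 50% |
|---|---|---|---|---|
| Risk ratio 0.33 | 46% | 67% | 83% | 93% |
| Odds ratio 0.33 | 40% | 53% | 64% | 70% |
| Odds ratio 0.31 (Introduction) | 42% | 57% | 68% | 74% |

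**Step 4: where 95% is reached.** As a risk ratio, at a control risk of about 52% with 45 per arm (49% with 50 per arm). As an odds ratio of 0.33, nowhere: a search over control risks peaks at about 73%, near a control risk of 64% (78% with 50 per arm). With the Introduction's 0.31 the peak is about 78% (82% with 50 per arm).

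**The case against.** **The scale of 0.33 is not established.** The odds ratio of 0.31 comes from another source and cannot settle what 0.33 is. This stands, and it is why both ratio scales are shown. Read as a risk difference, 0.33 with 45 per arm would give about 97%, 95% and 90% at control risks of 40%, 45% and 60%. That reading requires a control risk above 33% and is no better documented than the others.

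**A reader might infer that 0.33 was entered in G*Power as a standardised effect in a four-group test.** This is plausible, since one effect size without event rates is what those procedures take. The text does not say so, and that calculation gives 162 to 164 or 158, not 180.

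**A reader might infer that the mismatch in N shows too small a trial.** It does not. If f = 0.33 were right, 180 would be slightly more than needed (96.9%). The failure to reproduce and the unsupported power are separate points.

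**A reader might conclude that the design cannot have 95% power.** That is too strong. With a risk ratio of 0.33 it is reached pairwise at a control risk of about 52%, in a four-arm chi-square at about 44.5%, and for pooled programmes against control at about 39.5%. Only the odds-ratio reading rules it out pairwise at every control risk.

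**Details may sit in a fuller protocol or analysis plan.** This is fair for the test, its sidedness and the baseline risk. It does not cover the stated result, because the article gives inputs and an output that do not agree under the standard four-group tests. Sizing a trial on one of two primary outcomes is common, so the absence of a length-of-stay calculation is not counted as an error. Nor does the document make success in all three programmes a formal success rule, so the chance of that is not counted either.

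**Conclusion.** Wrong as written, in a conditional form. The figure of 180 does not follow from an effect of 0.33, alpha 0.05 and 95% power under the standard four-group tests, which give 162 (164 with equal arms) or 158. For PPC in each programme against usual care, 95% power is unsupported. It needs either a risk ratio with about half of controls having a PPC, or a reading of 0.33 that the article does not state. At assumed control risks of 20% to 40%, power is 46% to 83% on the risk-ratio reading and 40% to 64% on the odds-ratio reading. These figures rest on 45 analysed per arm, two-sided alpha 0.05, no multiplicity adjustment and assumed control risks. An adjustment for three comparisons would lower them: at alpha 0.05/3 and a risk ratio of 0.33, power is 30% at a 20% control risk and 50% at 30%.

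**What to change.** Keep 200 patients. In section 2.13, replace the 95% statement with the power, or the detectable difference, for each programme against control on PPC with 45 analysed per arm. State:

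1. the scale of 0.33 as given in its source;
2. the test and its sidedness;
3. an assumed control PPC risk with a range.

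The cost is one reworded paragraph and a less favourable stated power. No extra patients are needed. A pooled contrast of all prehabilitation arms against control, and a statement of the precision for length of stay, are optional additions and not part of this correction.

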### Statistical analysis

2.14

A framework for testing superiority will be applied. In the primary analyses, we will compare the effectiveness of both exercise interventions to usual care (no exercise training). Final analyses will be conducted after the collection and processing of data for the primary and secondary outcomes. The time points for data collection of each outcome are outlined in the outcomes section.

### Data management and sharing

2.15

After signing the informed consent form, each participant will be assigned a unique code number to safeguard their data and minimize the risk of unauthorized access or disclosure. Any information that links the pseudonym to identifiable details will be stored separately and managed to ensure it cannot be traced back to any individual.

The study will prioritize governance, ethical considerations, and comprehensive trial oversight. The protocol, plan for statistical analyses, and data management strategy will be openly accessible. Whether positive, negative, or inconclusive, results will be disseminated through peer-reviewed journals and presented at national and international conferences. The collected data will undergo double verification by a research team member.

## Discussion

3

Despite differing intervention strategies, prehabilitation consistently proves effective in bolstering patients' functional capacity [38]. Given that systemic inflammation and surgical stress commonly lead to reduced postoperative functional capacity—a major predictor of morbidity and mortality after lung surgery—optimizing physiological reserves preoperatively is crucial [39].

This need for enhanced physiological reserves is particularly relevant given that physical inactivity presents a significant global health challenge, disproportionately affecting older adults and leading to rapid deterioration of aerobic capacity and functional fitness and increased susceptibility to chronic illnesses. This inactivity can amplify the risk of post-surgical complications, particularly during major procedures [40]. Fortunately, studies demonstrate that preoperative exercise programs are effective in improving exercise capacity among lung cancer patients scheduled for surgical resection [41].

A recent systematic review and meta-analysis found that cancer patients with higher muscle strength or cardiorespiratory fitness levels had a significantly lower risk of all-cause mortality compared to those with lower physical fitness levels. Additionally, muscle strength and cardiorespiratory fitness were strong predictors of mortality, especially in patients with advanced cancer, and physical fitness components were also linked to a reduced mortality risk in lung and digestive cancers [42].

Prehabilitation may also help strengthen the respiratory muscles that affect functional capacity lung function, and cough effectiveness after thoracic surgery, consequently improving functional capacity [39].

Regarding the value of inspiratory muscle training, especially when applied in the preoperative period and pulmonary surgery, it was shown in a meta-analysis that it is effective in reducing PPC and LOS in patients undergoing surgery [43].

Evidence suggests that prehabilitation offers potential economic advantages by reducing complications, shorter hospital stays, and better patient outcomes. Assessing the economic impact of integrating prehabilitation programs, alongside their effectiveness for lung cancer patients, requires a comprehensive evaluation of the costs involved in improving care quality and the costs associated with program implementation [38]. This includes treatment expenses and the costs borne by healthcare providers [38], because effective prehabilitation programs require a multidisciplinary approach, integrating expertise from various healthcare professionals across different sectors [9].

The clinical implications of improving respiratory muscle function extend beyond the prevention of PPC. Our study seeks to validate how targeted prehabilitation can directly impact the use of hospital resources, given that previous data indicate that the combination of MIP%, MEP, and TLC% can explain 59% of the variation in LOS [44].

By comparing different training programs, our study aims to identify which intervention strategies can lead to more effective prehabilitation strategies, resulting in cost-effective and personalized treatments for lung cancer patients.

Although the effectiveness of prehabilitation programs is increasingly documented, there is a relative scarcity of studies investigating the costs associated with these interventions [45].

Based on these findings, our study will analyze the effects of the applied prehabilitation programs and their inherent costs.

### Strengths and limitations

3.1

This study possesses several notable strengths that enhance the reliability and validity of its findings. Firstly, the RCT design ensures rigorous participant allocation, minimizing selection bias and bolstering the validity of causal inferences. Secondly, the comprehensive assessment of functional capacity provides a holistic view of patient health. Thirdly, including PROMs, captures the patient's subjective experience, providing a well-rounded understanding of the intervention's impact. Fourthly, monitoring heart rate and oxygen saturation during exercise sessions allows for detailed adherence and physiological response analysis. Fifthly, the standardized pre- and post-operative care protocols and controlled warm-up, cool-down, and exercise program duration strengthen the attribution of observed effects to the exercise intervention. The study's mechanistic approach offers insights into how lifestyle and daily habit changes influence patient health and whether the intervention is sufficient to elicit positive post-operative changes. Finally, this study addresses a clinically relevant question, specifically evaluating the comparative effectiveness of different prehabilitation modalities and identifying potential superior interventions.

The study has some limitations that need to be considered. Although it may influence the results, including patients in neoadjuvant therapy will be controlled by statistical analysis. Risk stratification, in turn, will be used as an analysis variable, and not as an exclusion criterion. The inclusion of only individuals without heart disease, although it may limit the number of participants, aims to isolate the effect of the intervention on pulmonary complications, minimizing the influence of comorbidities. The relatively short duration of the intervention (2 weeks), although it may be sufficient for physiological changes, may not be ideal for long-term adaptations. However, it is important to remember that this period was defined so there would be no delays in the patient's surgery. The absence of blinding, justified by the nature of the intervention, will be mitigated by standardizing procedures and using independent evaluators. These limitations, however, are balanced by the strengths of the study.

## Data Availability

No data was used for the research described in the article.
